##### Outcome assessment

From eCAP data, we construct an index of *medication adherence intensity* (MAI) at *t=* 6 and 12months from the amount of medication taken, relative to the total amount of medication prescribed. This is a fractional outcome with values in the range [0, 1], with value 1 for perfect adherence and value 0 for no adherence at all. In the baseline period, 3months prior, for which eCAP data will not be available, a proxy measure will be used. Construction of MAI: The period (0, *t*] is partitioned into intervals, *k*=1,…*K* where *t*_0_ = 0, *t*_*K*_ = *t*. In the interval (*t*_*k* − 1_, *t*_*k*_]we obtain the total prorated amount prescribed (*f*_*k*_) and the actual amount taken (*m*_*k*_). The adherence for this interval and for the period (0, *t*] is a time-weighted proportion [28].

##### Patient Activation Measure (PAM)

PAM is a continuous score on a 0–100 scale. Higher scores are associated with better activation [71, 72]. For MAI as continuous response, the beta regression model [73] with logit link posits the conditional mean and variance where *f*<1 is the under-dispersion. For PAM as continuous response, we will use a linear mixed model with mean and variance. Methods for the UKPDS risk score and patient engagement are entirely analogous. The structural forms of and are elicited from preliminary analyses of residuals [64]. Estimation of model parameters is via full maximum likelihood (ML), quasi-ML or restricted ML [64].

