### Outcomes {12}

All data will be collected at baseline, 6 months, and 12 months (Table 2). Our primary outcome is medication adherence measured using eCAP electronic monitoring and self-report. Secondary outcomes are (a) diabetes-specific 5-year CVD risk as measured with UK Prospective Diabetes Study (UKPDS) Engine score; (b) provider engagement as measured by CollaboRATE Shared-Decision Making measure; and (c) patient activation measures (PAM).

**Table 2 Tab2:** Measures table

Variables	Instruments	Methods	Analysis	Time
**Knowledge and attitude about patient-centered care, SDM, use of DSTs**	**Pre and post survey of providers** **Semi-structured interviews**	**90 min. CME interactive orientation sections with providers and exit interviews**	**Descriptive pre-post analysis** **Thematic analysis of transcribed interviews using Dedoose**	**Pre and post physician education** **End of study**
**Medication adherence**	**Medication Events Monitoring Systems ( eCap).** **Cronbach’s alpha=.0.85** **ARMS Survey**	**eCap upload to BRIC** **RA will administer form to patient pre/post intervention to evaluate treatment medication adherence**	**Linear or generalized linear mixed effects model and Beta regression to evaluate changes over time for groups 1 and 2**	**Baseline, 6 and 12 months**
**Patient Activation Measure Scores/Level**	**Patient Activation Measure (PAM) Cronbach’s alpha=.91**	**RA administers form to patient pre and post intervention**	**Linear or generalized linear mixed effects model for change overtime for groups 1 and 2**	**Baseline, 6 and 12 months**
**Self-Efficacy Scores**	**Stanford 6-Item Self Efficacy Scale** **Summary DM Self-Activities Measure (SDSCA)**	**RA administers form to patient pre and post intervention to evaluate change in self-efficacy**	**Linear or generalized linear mixed effects models for change over time for groups 1 and 2**	**Baseline, 6 and 12 months**
**Rate of use of aspirin/antiplatelets, beta-blockers, ACEI/ARBs, cholesterol assessment and treatment, DM medications**	**PAI agreement in chart** **Patient medication list** **Patient medical record** **Texting log**	**Chart audits to compare the rate of use of aspirin/antiplatelets, beta-blockers, ACEI, cholesterol assessment and treatment of DM**	**Linear or generalized linear mixed effects model for change overtime for groups 1 and 2**	**Baseline, 6 and 12 months**

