### Methods in analysis to handle protocol non-adherence and any statistical methods to handle missing data {20c}

#### Addressing missingness [82]

In linear and nonlinear mixed models, likelihood-based inference using only the non-missing responses is valid under missing at random (MAR). Missing completely at random is likely to be untenable in our context. Techniques such as inverse-probability weighting will be used to accommodate missing data patterns that are neither MCAR nor MAR [83–85], an approach that we used in analyzing longitudinal censored medical costs data [85, 86].

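### The adherence index may equal exactly 0 or 1, but the beta regression named for it has no usable likelihood there, and the plan fixes neither a boundary rule nor the estimator.

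*Protocol article*

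**What the plan says.** All references are to the protocol article.

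- **Outcome assessment** (Statistical methods {20a}) builds MAI from eCAP data at 6 and 12 months and calls it a "fractional outcome with values in the range [0, 1], with value 1 for perfect adherence and value 0 for no adherence at all". The endpoints are therefore declared values of the outcome.
- **Patient Activation Measure (PAM)**, same section, assigns the model: "For MAI as continuous response, the beta regression model [73] with logit link posits the conditional mean and variance", with a factor f below 1 that "is the under-dispersion".
- After covering MAI, PAM, the UKPDS score and patient engagement, the same paragraph adds: "Estimation of model parameters is via full maximum likelihood (ML), quasi-ML or restricted ML". It does not say which estimator belongs to which outcome.
- **Table 2** (Outcomes {12}) gives for medication adherence: "Linear or generalized linear mixed effects model and Beta regression to evaluate changes over time for groups 1 and 2".
- **Addressing missingness** states that "likelihood-based inference using only the non-missing responses is valid under missing at random (MAR"). This concerns responses that were not observed. It does not cover an observed 0 or 1 that the model cannot evaluate.

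The text contains no rule for exact 0s and 1s in the beta model. It also contains no statement that such patients are excluded.

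**The concern.** The outcome definition and the named model do not fit together. The beta density has support on (0, 1). At exactly 0 or 1 its logarithm is plus or minus infinity, apart from the special case of a shape parameter equal to 1. A full-likelihood fit therefore needs those records removed, moved or modelled separately.

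Removal would select patients on the primary outcome itself. Those removed would be the perfect adherers and the complete non-adherers, and their shares would probably differ between arms if the intervention works. The comparison would no longer be between the groups as randomised.

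The routes open to the analyst (interior values only, squeezing values inwards, quasi-likelihood on all values) can give different primary estimates from the same data. The article states under Who will be blinded? {17a} that the researchers are not blinded, so the route should be fixed before outcome data are seen.

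**Working it through.** **The plan's own figure.** The article gives no boundary share and no distribution for MAI, so there is no stated figure to reproduce. Sample size {14} gives hypothesised 12-month adherence of 0.65 in group 1 and 0.42 in group 2, with 9 and 8 teams and 320 evaluable patients. Splitting 320 by 9:8 gives 169 and 151. The hypothesised difference is 0.65 − 0.42 = 0.23. On the logit scale it is ln(0.65/0.35) − ln(0.42/0.58) = 0.619 + 0.323 = 0.942.

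**Step 1: can the likelihood use 0 and 1?** With mean μ and precision φ the shape parameters are μφ and (1 − μ)φ.

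| μ | φ | shapes | log-density at 0 | log-density at 1 |
|---|---|---|---|---|
| 0.42 | 2 | 0.84, 1.16 | +∞ | −∞ |
| 0.65 | 2 | 1.30, 0.70 | −∞ | +∞ |
| 0.42 | 5 | 2.10, 2.90 | −∞ | −∞ |
| 0.65 | 5 | 3.25, 1.75 | −∞ | −∞ |

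A standard beta-regression routine refused a simulated data set holding 9 zeros and 24 ones. The quasi-likelihood fractional logit fitted all 320 records of that set.

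**Step 2: how many patients, and what happens to the estimate?** Assumed model: adherent days out of 180 are beta-binomial with means 0.65 and 0.42, n = 169 and 151, clustering ignored, 300 runs for each φ. The precision φ is an assumption.

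| φ | mean number at 0 or 1 (of 320) | share | beta ML, interior values only | quasi-ML, all values | true |
|---|---|---|---|---|---|
| 1 | 36.3 | 11% | 0.62 | 0.94 | 0.942 |
| 2 | 7.5 | 2.3% | 0.84 | 0.94 | 0.942 |
| 5 | 0.2 | 0.07% | 0.94 | 0.94 | 0.942 |

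The shortfall is (0.942 − 0.621)/0.942 = 34% at φ = 1, (0.942 − 0.844)/0.942 = 10% at φ = 2, and nil at φ = 5.

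A separate run of 200 replicates added beta regression after squeezing values slightly inwards. At φ = 1 it gave 0.63 (interior only), 0.87 (squeezed) and 0.94 (quasi-ML). At φ = 2 it gave 0.86, 0.95 and 0.95.

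**Step 3: cross-check by hand.** If a share p1 sits at 1 and p0 at 0, the mean of the remaining patients is (mean − p1)/(1 − p1 − p0). The 180-day model at φ = 1 has p1 = 0.1172, p0 = 0.0134 in group 1 and p1 = 0.0233, p0 = 0.0734 in group 2.

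- Group 1: 0.5328/0.8694 = 0.613. Group 2: 0.3967/0.9033 = 0.439.
- The log-odds difference of these interior means is 0.70.

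Exclusion alone thus moves 0.94 to 0.70. Fitting a beta likelihood to the truncated values takes it on to 0.62. The same calculation at φ = 2 gives 0.88, against 0.84 from beta ML.

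**Step 4: is the direction fixed?** The same formula with other assumed shares, written as ones/zeros:

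| Group 1 | Group 2 | interior means | difference (true 0.23) |
|---|---|---|---|
| 10%/5% | 5%/10% | 0.647, 0.435 | 0.21 |
| 20%/5% | 10%/10% | 0.600, 0.400 | 0.20 |
| 25%/5% | 10%/15% | 0.571, 0.427 | 0.145 |
| 10%/10% | 10%/10% | 0.6875, 0.400 | 0.29 |
| 15%/8% | 10%/10% | 0.649, 0.400 | 0.25 |

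The last row has more ones and fewer zeros in group 1, as expected if the intervention works, yet the difference grows.

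**Step 5: length of the window.** MAI covers the whole period from 0 to t, and exact 0s and 1s become rarer as it lengthens. Over 365 days at φ = 1 the model gives 169 × 0.1001 + 151 × 0.0701 = 27.5 patients (8.6%). At φ = 2 it gives 169 × 0.0183 + 151 × 0.0085 = 4.4 (1.4%).

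**The case against.** The best defence is that the article already contains a workable route. It describes the MAI model by a conditional mean and variance with a logit link, and it lists quasi-ML. Quasi-likelihood with a logit mean and a variance proportional to μ(1 − μ) is the fractional logit, which accepts 0 and 1 and recovered the true value in every setting tried. Table 2 also names linear or generalized linear mixed models beside beta regression. The mean and variance expressions themselves are missing from the text as read, and boundary handling is a detail that an article often leaves to the analysis plan, which is not shown.

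Much of this stands. A reader might infer that perfect adherers and complete non-adherers will be lost from the primary analysis. The article does not say so: it states no exclusion, and one of its listed estimators would keep them. A reader might also infer that the error must run towards no effect. The last two rows of the direction table show that it need not.

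The mismatch itself remains. The outcome range and the model are both stated, not left open, and the model as named does not cover that range. Listing three estimators for four outcomes without assigning one to MAI leaves the matter unsettled. The article does provide for excess zeros elsewhere, with zero-inflated and two-part models for utilisation and cost in Aim 3, but makes no such provision for the primary outcome.

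**Conclusion.** The concern holds as an internal conflict with an open choice. MAI admits 0 and 1; beta regression fitted by full ML does not; the estimator that would resolve this is listed but not assigned. Severity is moderate.

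The size cannot be fixed from the documents. In the simulation it runs from a one-third understatement of the log-odds difference (φ = 1, about 11% of patients at the boundary) to nothing (φ = 5, below 0.1%). These figures rest on an assumed precision, a beta-binomial shape, a 180-day window combined with the hypothesised 12-month means, and no clustering. Over a full year the boundary shares would be smaller. The understatement seen there belongs to those assumptions and is not a general direction of bias.

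A ruling that the primary analysis is invalid as written would go too far, because a valid fit is available within the listed estimators.

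**What to change.** State one primary model and one estimator for MAI that admit 0 and 1. Either of these would do:

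- a fractional logit fitted by quasi-ML on all MAI values; or
- a binomial mixed model with overdispersion on adherent days out of expected days.

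In both cases keep the within-team and within-patient correlation that the article already requires. Move beta regression to a sensitivity analysis in zero-one-inflated form, and report the number of patients at exactly 0 and 1 by arm and time point. Make the same choice in Table 2 and in Statistical methods {20a}.

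The cost is one changed model statement and matching wording. No new data are needed. It should be settled before outcome data are examined.

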##### Moderators and mediators

By including terms for potential confounders (e.g., gender, education, race/ethnicity) in the covariate mix, we will assess whether their inclusion substantively changes the magnitude of the treatment-outcome effect by examining the change in the regression coefficients for study arms. We will characterize the study results for males and females and determine the impact of sex on the intervention uptake and outcomes. A simple mediation analysis posits that some 6-month outcomes (e.g., patient activation, provider-prescribing for secondary prevention of CVD) might influence the 12-month outcomes. We will initially adopt the systems-equation approach of Baron-Kenny [74] and MacKinnon et al. [75, 76] before examining more complex models for multiple mediating and confounding effects informed by directed acyclic graphs [77].

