## Objectives {7}

We hypothesize that the combined intervention will improve both patient adherence and clinical outcomes over 12 months. We will randomize 17 teams in 12 FQHCs, recruiting 378 adults with T2DM to either (1) Office-GAP + Texting or (2) Texting only. Our primary outcome is medication adherence measured using eCAP electronic monitoring and self-report. Secondary outcomes are (a) diabetes-specific 5-year CVD risk as measured with the UK Prospective Diabetes Study (UKPDS) Engine score, (b) provider engagement as measured by the CollaboRATE Shared-Decision Making measure, and (c) patient activation as measured by the Patient Activation Measure (PAM).Aim 1: Compare the effects of Office-GAP + Texting intervention (group 1) with Texting only (controlling for attention) (group 2) in improving medication adherence, UKPDS risk score, provider engagement, and patients’ activation scores. Hypotheses:H1: Group 1 patients will show significant improvement compared with group 2 at 6 and 12 months in the (a) primary outcome of medication adherence, (b) secondary outcomes of UKPDS score, (c) provider engagement, and (d) patient activation scores.Aim 2: Identify barriers and facilitators to adoption, implementation, maintenance, and spread using an integrated RE-AIM and Consolidated Framework for Implementation Research (CFIR) and to explore potential mediators and moderators of effectiveness.Exploratory aim 3: Determine whether there are differences in cost and health care utilization between groups 1 and 2 using the Micro-Costing Questionnaire and The Health Services Utilization Form.

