#### Surveys (Table 2)

Completed at 0, 6, and 12 months: (a) CollaboRATE Shared-Decision Making measure: CollaboRATE, a fast and frugal patient-reported measure of SDM process, contains 3 brief questions that patients complete following a clinical encounter [53, 54] and has inter-rater reliability of .86 at .001 significance. (b) Patient Activation Measure: The Patient Activation Measure (PAM) consists of 13 items that form a scale with a Cronbach’s alpha of .9 [55]. (c) Combined Outcome Measure for Risk Communication And Treatment Decision Making Effectiveness (COMRADE) [56] measures patient satisfaction with physician communication, and patient confidence in decisions made. This scale has good internal consistency (Cronbach’s alpha=.92); (d) Stanford Self-Efficacy Scale for Managing Chronic Diseases – 6-Item Scale with internal consistency of reliability of .91 [57]. (e) Summary of Diabetes Self-Care Activities (SDSCA) Measure, a multidimensional measure of DM self-management; with good internal and test-retest reliability [58]. (f) the Rapid Estimate of Adult Literacy in Medicine (REALM) [59], a widely used measure of health literacy [60] tailored to poor medication adherence [61].

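### The 12-month adherence index starts at baseline, so in a mediation model with a 6-month mediator about half of the outcome precedes the mediator

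*Protocol article*

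**What the plan says.** Aim 2 in the protocol article (Objectives {7}) includes a plan "to explore potential mediators and moderators of effectiveness". The section Moderators and mediators gives the method. It posits that "some 6-month outcomes (e.g., patient activation, provider-prescribing for secondary prevention of CVD) might influence the 12-month outcomes". The first step is named: "We will initially adopt the systems-equation approach of Baron-Kenny", with a companion reference to the same family of methods. This is done "before examining more complex models for multiple mediating and confounding effects informed by directed acyclic graphs". The section lists no covariates for the mediation equations and no rule for calling a variable a mediator.

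The section Outcome assessment defines the MAI from eCap data at t = 6 and 12 months. The period from 0 to t is cut into intervals, and "The adherence for this interval and for the period (0, *t*] is a time-weighted proportion". The 12-month index therefore runs from baseline to month 12. For the three months before baseline, "for which eCAP data will not be available, a proxy measure will be used".

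The surveys, PAM among them, are "Completed at 0, 6, and 12 months".

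**The concern.** A mediator can only affect what comes after it. The 12-month MAI averages adherence over months 0-12, and PAM as mediator is read at month 6, so 6 of the 12 months in the outcome were already past. Randomising teams protects the comparison of arms on PAM. It does not protect the association between PAM and adherence within arms. If good early adherence raises 6-month PAM, the early half of the outcome is correlated with the mediator by construction, and the equations read that as an effect of PAM on adherence.

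The trial expects Office-GAP to raise PAM (hypothesis H1(d)), so the arm-to-mediator path is likely to be significant. The conclusion then turns on the PAM-adherence association alone. The error runs in one direction, towards confirming the activation mechanism on which the intervention is based. What is at stake is the trial's account of how Office-GAP works. The test of whether it works is not affected.

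**Working it through.** The protocol states no figure for the mediation analysis, so there is none to reproduce. The calculation below is an illustration.

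**Inputs from the protocol.** There are 320 evaluable patients and 9 versus 8 teams, giving 320 × 9/17 ≈ 169 and 320 × 8/17 ≈ 151. The serial correlation is 0.30, used here for early versus late adherence. Tests are two-sided at 5%. The ICC is 0.002. With 320/17 ≈ 18.8 patients per team the design effect is 1 + 17.8 × 0.002 ≈ 1.04, so clustering is ignored.

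**Assumptions not in the protocol.** The arm effect on PAM is a = 0.3 or 0.5 SD. The within-arm correlation of 6-month PAM with months 0-6 adherence is ρ = 0.1, 0.2 or 0.3. PAM has no effect on adherence. A mediator is flagged when both paths (arm to PAM, and PAM to adherence given arm) have p < 0.05.

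**Step 1, arm to PAM.** The standard error is √(1/169 + 1/151) = 0.112. At a = 0.3, z = 2.68 and the path is significant with probability 0.764. At a = 0.5, z = 4.47 and the probability is 0.994.

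**Step 2, PAM to adherence within arm.** Let E be months 0-6 adherence and L months 6-12 adherence, each with unit variance and correlation g = 0.30.
- Cumulative outcome (E + L)/2: the correlation with PAM is ρ√((1 + g)/2) = 0.806ρ, that is 0.081, 0.161 and 0.242.
- L alone: the correlation is ρg, that is 0.03, 0.06 and 0.09.
- L adjusted for E: the correlation is 0.

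With about 317 degrees of freedom, z ≈ r√317/√(1 − r²). For the cumulative outcome this gives 1.44, 2.91 and 4.44, so the path is significant with probability 0.30, 0.83 and 0.99. For L alone it gives 0.53, 1.07 and 1.61, and probabilities 0.08, 0.19 and 0.36. Adjusted for E, the probability is 0.05.

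**Step 3, both paths significant** (product of steps 1 and 2, for a = 0.3 to a = 0.5):

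| Outcome in the mediation model | ρ = 0.1 | ρ = 0.2 | ρ = 0.3 |
|---|---|---|---|
| MAI over 0-12 months | 23-30% | 63-82% | 76-99% |
| MAI over 6-12 months, unadjusted | 6-8% | 14-19% | 28-36% |
| MAI over 6-12 months, adjusted for 0-6 | 4-5% | 4-5% | 4-5% |

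Simulated trials under the same assumptions agree: 22-31%, 61-82% and 77-99% for the cumulative index, 7-32% overall for months 6-12 unadjusted, and 4-5% after adjustment. The middle row shifts by a few points with the scaling of the error terms.

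**Boundary cases.** If the arm does not move PAM, step 1 succeeds in only 5% of trials. If ρ = 0, step 2 succeeds in only 5%. Either way the joint rate is about 5% or less.

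**Do baseline covariates help?** With baseline PAM and a baseline adherence proxy added but the 0-12 month outcome kept, simulation still gives about 24-34%, 61-88% and 72-99.6% at a reverse effect or correlation of 0.1, 0.2 and 0.3. The outcome window drives the error.

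**Where must months 0-6 MAI not go?** It is affected by arm. If early adherence carries an arm effect of 0.5 SD, adding it to the mediator equation changes the arm coefficient from a to a − 0.5ρ. At a = 0.3 and ρ = 0.3 that is 0.30 − 0.15 = 0.15, half the randomised effect.

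**The case against.** The strongest reply is that the protocol fixes little here. A reader might infer that the equations leave out baseline activation and earlier adherence. The text does not say so. It lists no covariates, PAM is collected at baseline, a baseline adherence proxy and a 6-month MAI are planned, and the covariates of an exploratory model are commonly left to the analysis plan. That objection stands, and no omission is alleged here.

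The section also plans models for confounding informed by directed acyclic graphs after the first step. That is to its credit, but nothing says those models would change the outcome window, and adjusting for confounders does not move an outcome to after its mediator.

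The 12-month outcomes are not named in the mediation section, and UKPDS risk, PAM, CollaboRATE and ARMS are not 0-12 month eCap averages. That also stands: the point is confined to MAI. MAI is the eCap form of the primary outcome, however, and its 12-month value has a stated definition.

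Finally, the joint-significance rule is mine. It is a standard reading of the named method, but the protocol states no rule and speaks only of exploring.

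**Conclusion.** The point holds for the adherence outcome. Under the stated definition, 12-month MAI begins six months before the mediator is measured, so reverse causation can appear as mediation. Under the assumptions listed, a mediator with no effect would be flagged in about 22-99% of trials, against 4-5% when months 6-12 MAI is adjusted for months 0-6 MAI.

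A reader might take the upper figures as an error rate of the plan. The documents do not support that: the arm effect on PAM, the PAM-adherence correlation and the decision rule are all assumed, and the rate is about 5% or less if either association is absent. Nor does the point touch the primary or secondary comparisons of arms. Severity is minor, because the mediation analysis is an exploratory part of Aim 2.

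**What to change.** In Moderators and mediators, specify for the adherence model:
- Outcome: MAI over months 6 to 12.
- Outcome equation: adjust for MAI over months 0 to 6, the baseline value of the mediator and the baseline adherence proxy.
- Mediator equation: adjust for baseline values only, not for months 0-6 MAI.
- Report a sensitivity analysis for residual mediator-outcome confounding.

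The last item is needed because the adjustment does not remove a shared trait behind activation and adherence. In simulation with such a trait, and with adjustment for baseline values and 6-month adherence, false flags remained at 7-13% for a trait correlation of 0.3 and reached about 56% at 0.8.

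The cost is wording and a re-cut of the eCap record, which is daily; no new data are needed. There are two statistical costs. The interval for the indirect effect will be wider. Activation effects already expressed before month 6 will not be credited, and that may be much of the effect: the projected rates give a difference of 0.62 − 0.42 = 0.20 at 6 months and 0.65 − 0.42 = 0.23 at 12 months, so 0.20/0.23 ≈ 87% of the projected separation is present by month 6. The report should say so.
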